## Abstract

Academic burnout is a condition characterized by exhaustion, cynicism, a distant attitude toward studying, and diminished self-efficacy in academic activities. Preliminary scientific findings indicate that interventions designed to alleviate work burnout also hold promise for mitigating academic burnout, however clear evidence based on randomized controlled trials is still missing. This research protocol describes a randomized controlled trial aimed at evaluating the efficacy of an online group psychological intervention to contrast academic burnout. Participants with high levels of burnout will be assigned to a psychological counseling group or a waiting list control group. The research comprises several phases: (T0) Screening, Recruitment, and Randomization; (T1) Baseline assessment (pre-intervention); (T2) Outcome Assessment (post-intervention); and (T3) Follow-up Assessment (3 months post-intervention). The primary outcomes include burnout symptoms, general wellbeing, and academic achievement. Additionally, secondary variables such as effort-reward imbalances, satisfaction/frustration of basic psychological needs, intrapersonal and interpersonal emotion regulation, coping strategies, and social support will be examined. The psychological intervention strategies will encompass psychoeducation, self-awareness enhancement, cognitive restructuring, and promotion of social support. This research protocol is an initial step toward evidence-based psychological interventions to treat academic burnout.

## Introduction

Burnout is a syndrome characterized by emotional exhaustion, depersonalization, and reduced personal accomplishment, traditionally attributed to chronic responses to occupational and interpersonal stress conditions at work (Freudenberger, 1974; Maslach, 1976). More recently, the concept of burnout has been extended to the educational context, where “academic burnout” is described as a condition characterized by exhaustion from studying, cynicism, distant attitude toward studying, and reduced self-efficacy in relation to academic activities (Schaufeli et al., 2002; Zhang et al., 2007). It is associated with a lower feeling of efficacy in tackling the course of studies (Rahmati, 2015), lengthening or interruption of the academic career (Madigan and Curran, 2021), as well as a higher incidence of psychological disorders (Deeb et al., 2018), substance abuse (Kadhum et al., 2022), suicidal ideation and suicide (Dyrbye et al., 2008).

The efficacy of psychological interventions to contrast work burnout has been largely demonstrated in several meta-analyses focused on general employees' categories (Maricutoiu et al., 2016; Ahola et al., 2017; Perski et al., 2017) and on more at-risk categories, such as health workers (Rahmati, 2015; Panagioti et al., 2017) and teachers (Iancu et al., 2018). Effective individual-centered interventions include awareness enhancing strategies - typically, self-monitoring of stress symptoms and psychoeducation on adaptive/maladaptive strategies to cope against stress—and arousal reductions strategies (for example, relaxation techniques and mindfulness meditation) (Le Blanc and Schaufeli, 2008). In more complex interventions, also strategies aimed at changing maladaptive cognitions have been successfully used (Le Blanc and Schaufeli, 2008; Bresó et al., 2011). Namely, negative cognitions concerning self-efficacy have been shown to play a key role, with high level of self-efficacy acting as a protective factor against burnout (Shoji et al., 2016).

To our knowledge, there is limited research on the efficacy of psychological interventions to treat academic burnout. Early scientific evidence suggests that psychological interventions to decrease work burnout are also promising for academic burnout. For instance, reduction of academic burnout scores has been documented after psychological counseling sessions to enhance self-awareness (Luo X., 2012; Luo Z. Y., 2012; Liu, 2013; Zhang et al., 2014; Guo, 2016; Shen, 2020), contrast maladaptive cognitions or “cognitive restructuring” (Ni and Wu, 2009; Xiong and Fang, 2017; Apriliya and Lianawati, 2023) or decrease stress related arousal (Ye et al., 2017; Wan, 2020).

In combination with individual-centered approaches, organizational approaches focused on enhancing social support may also be effective. Indeed, social support has both indirect (buffering) and direct effects in the relationship between stressors (e.g., academic demands) and students' burnout (Kim et al., 2018; Kusuma et al., 2022). Furthermore, strategies of interventions based on the provision of supportive relationships in the academic context could be useful to decrease students' burnout (Ezenwaji et al., 2019; Xu, 2019). Beyond specific strategies to enhance social support, the provision of psychological interventions in a group format could represent a natural source of social support (Biolcati et al., 2017; Brusadelli et al., 2020). Together with advantages in terms of social support provision, psychological interventions at the group level are the most suitable approaches for organizational settings. Indeed, group counseling is widely used in academic burnout interventions (Tang et al., 2021). More recently, early documentation of the efficacy of online group psychological counseling to treat academic burnout has been also provided (Eseadi, 2022; Apriliya and Lianawati, 2023).

In summary, early studies support the hypothesis that psychological interventions are useful to contrast academic burnout. Among others, interventions focused on self-awareness, cognitive restructuring, and social support are promising. Interestingly, there is also preliminary evidence that combining two or more strategies in integrated approaches could add value in terms of effectiveness of such interventions (Tang et al., 2021). However, the number of existing studies is still exiguous and available studies present relevant methodological limitations, above all the lack of adequate of control conditions (Tang et al., 2021). Moreover, the studies described above come almost exclusively from Asia and the adaptation to different cultural context cannot be taken for granted. Thus, more research is required in the direction of validating psychological interventions to treat academic burnout.

In the present research protocol, we propose a randomized controlled study designed to test the efficacy of an online group psychological intervention protocol to contrast academic burnout. We opted for Transactional Analysis (TA) as the theoretical background of this intervention (Berne, 1961; Vos and van Rijn, 2021). Even if TA has received limited attention by psychotherapy research, it is widely taught and practiced internationally within recognized academic and professional institutions (Vos and van Rijn, 2022), and it has a large history of application in organizational settings in Europe and United Kingdom (for organizational TA manuals see: Davidson and Mountain, 2016; Cannavale and Castagna, 2018; van Poelje and de Graaf, 2021). The main advantage of TA-based interventions for burnout lies in its intrinsic combination of individual and organizational approaches (Thunnissen and Timmermans, 2023), due to the simultaneous focus on human personality (focus on intra-personal processes) and social behavior (focus on interpersonal processes (Berne, 1961). This double focus is evident in the traditional group format of TA in its origins (Berne, 1958). Finally, TA treatments were one of the first models of psychological intervention that integrated cognitive-behavioral approaches with psychoanalytic concepts, developing a substantive new theory, as a strategy for integration (Vos and van Rijn, 2023). Thus, it is a flexible model, easily adaptable to the integration of different strategies of intervention, as in the psychological counseling program tested in the present research protocol.

### Aims, hypotheses, and study design

The present study is a randomized clinical trial aimed at generating evidence in support of the effectiveness of an online group psychological counseling intervention in university students with high levels of academic burnout. To this aim, the study design entails the comparison between students that will be randomly assigned to two matched groups: (1) a psychological counseling group (PC, *N* = 65) or (2) a waiting list control group (WL, *N* = 65). We will test the effect of time (pre-PC vs. post-PC) in interaction with the effect of group (PC vs. WL) on the score obtained in several self-report outcome measures, including scores on burnout symptoms, general wellbeing, and academic achievement as primary outcomes. We hypothesize that PC, compared to WL, should provide evidence of the efficacy of psychological counseling to decrease burnout symptoms and improve general wellbeing and academic achievement.

Moreover, to acquire data on possible mediators or psychological change, we will also assess a large set of secondary outcome variables potentially related to academic burnout, including effort-reward imbalances, basic psychological needs of satisfaction/frustration, intrapersonal and interpersonal emotion regulation, coping strategies and social support. Such variables will be directly and/or indirectly addressed in the psychological counseling sessions (see Section “Intervention” and Table 1). We hypothesize that secondary outcomes variables may be affected by the psychological counseling intervention, mediating or moderating its effects on primary outcomes.

**Table 1 T1:** Summary of psychological counseling intervention features.

**Session**	**Strategy**	**In-session activities**	**Treatment goals**	**TA techniques**
First	Psychoeducation	Information provision on stress, burnout, and coping Information provision about intervention action and goals	Self-awareness	Contract
	Agreement treatment goals	Set goals for time in treatment	Self-awareness	
	Promotion of social support	Introduction of participants and personal experiences sharing	Social support	Therapeutic alliance/group cohesion
Second	Psychoeducation	Information provision on psychological basic needs Identification of basic needs and their satisfaction or frustration in the academic context	Self-awareness	Strokes Therapeutic alliance/group cohesion
	Promotion of social support	Experiential exercise of need satisfaction in the group Identification of adaptive ways to ask for social support	Social support	
Third	Promote self-awareness of personal reactions to stressful events.	Identifications of personal reaction (thoughts, emotions, somatic sensations, behaviors) to specific stressful events in the academic context.	Self-awareness	Ego states identification
	Promote self-awareness unhelpful reactions and development of more helpful reactions to stressful events.	Identification of unhelpful reactions to specific stressful events in the academic context, and initial development of more helpful reactions.	Cognitive restructuring	Ego states decontamination
Fourth	Promote self-awareness of mental representations of self and others.	Identifications of thoughts about the self and the other in the academic context (for example professors, university technical staff, or other students) and the related emotions, somatic sensations, and behaviors.	Self-awareness	Existential positions
	Development of helpful mental representations of self and others.	Explore the options for alternative mental representations of self and others.	Cognitive restructuring	
Fifth	Promote self-awareness of automatic behaviors.	Identifications of learning styles. Explore the options for alternative learning styles.	Self-awareness	Drivers
Sixth	Program review	Identify positive outcomes for each individual and areas they still want to work on.	Self-awareness	Contract completion
		Identify positive relationships in the group and future plans.	Social Support	

The research protocol was registered on ClinicalTrial.gov on January 2024 (protocol 9-FIN/RIC).

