### Participants and sample size

Assuming a medium effect size (Cohen's *d* = 0.50), we estimated with the G^*^Power3 software (Faul et al., 2007) that we need a sample size of 128 participants (i.e., two groups of 64 students) to achieve a power of 0.80 (α = 0.05). Thus, a total of 130 students will be recruited from bachelor's courses at Universitas Mercatorum. Participants are eligible for inclusion according with the following criteria: (a) age > 18 years; (b) clinical levels of academic burnout scores [one standard deviation above the mean MBI-SS total score reported in the validation study by Portoghese et al. (2018)]; (c) attendance of 1^st^ or 2^nd^ year of bachelor course at Universitas Mercatorum; and (d) sufficient knowledge of the Italian language. Additional exclusion criteria aimed at selecting a sufficiently homogeneous group of participants are: (a) previous university degree; (b) other psychiatric diagnoses; (c) other ongoing psychological or psychiatric treatments. Finally, we also excluded (d) attendance of 3^rd^ year of bachelor course, to avoid participants drop-outs due to the course conclusion.

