### Statistical analysis

Descriptive statistics will be reported for participant recruitment, acceptance, adherence, and dropout rates. Baseline characteristics for each group will be reported to ensure group matching on these variables. To verify the reliability of the eight questionnaires, we will compute test-retest correlations between T1 and T2, and between T1 and T3 (using Pearson's *r* coefficients).

To assess the effects of PC on the outcome variables (MBI-SS, PGWB-S, and academic achievement), mixed model regressions will be utilized, by considering Time (T1, T2, and T3) and Group (PC vs. WL) as fixed factors and subjects as the random factor. This technique will allow us to test the interaction between Time and Group. Our expectation is that PC and WL should differ at T2 and T3, but not at T1, indicating that the PC group should achieve higher scores than the WL group after, but not before, the psychological counseling intervention.

A series of path analyses will be conducted to determine whether the measures obtained from the BPNSFS, ERI-SQ, CERQ-18, DIRE, Brief-Cope, and MSPSS questionnaires mediate the differences in the outcome variables between T1 and T2, and T1 and T3. For each analysis, the exogenous variables will be the outcome measures at T1, the mediators will be the scores in the subscales of the BPNSFS, ERI-SQ, CERQ-18, DIRE, Brief-Cope, and MSPSS questionnaires, and the endogenous variables will be the outcome measures at T1. Since each questionnaire involves multiple subscales, two separate models will be computed for each mediator. For example, for the BPNSFS questionnaire, we will test whether the Autonomy Satisfaction, Competence Satisfaction, Relatedness Satisfaction, Autonomy Frustration, Competence Frustration, and Relatedness Frustration subscales will mediate the associations between the T1 and T2 (or T1 and T3) outcome measures.

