We will also calculate Reliable Change Index (RCI) and Clinically Significant Change (CSC) (Jacobson and Truax, 1991) for each patient, from pre- to post- treatment and at follow-up. The RCI is computed as a ratio in which the numerator represents the difference between each subject's pretest and post-test outcome scores, while the denominator represents the standard error of the difference between the two test scores. According to Jacobson and Truax (1991), RC indices larger than 1.96 indicate that a significant change has occurred. The CSC is represented by a patient's score moving from the “dysfunctional population” range into the “functional population.” For example, pre-treatment to post-treatment of at least 2 standard deviations from the original mean (Evans et al., 1998). Finally, we will provide grouped percentages (PC vs. WL) for those individuals who reliably improved or had a clinically significant change.

The study is based on substantial evidence that psychological interventions promoting self-awareness, cognitive restructuring, and social support are effective strategies to combat burnout. This provides a strong foundation for the research. The study applies these interventions to the specific case of academic burnout, a field that is promising but still lacks strong evidence from randomized controlled trials. In the present article, we described the research protocol of the first randomized controlled trial to determine the efficacy of an online group psychological intervention specifically designed for university students with high levels of burnout. Moreover, we gave attention to several methodological issues. In line with the empirically supported psychological treatments requirements (Chambless and Hollon, 1998), we propose a between-group design with adequate statistical power, and we clearly specified sample characteristics (defined by standard measures). We also identified a large range of possible primary and secondary outcomes, and we planned the implementation of statistical analyses suitable for the understanding of different levels of effects in the data that will be collected.

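### Three co-equal primary domains (5 to 7 scores) have no ranking, primary time point or success rule, while 128 participants give 0.80 power for one test only

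*Protocol article*

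**What the plan says.** The section on aims, hypotheses and study design compares counseling (PC) with waiting list (WL) on several self-report measures, "including scores on burnout symptoms, general wellbeing, and academic achievement as primary outcomes". The abstract and the section on primary outcome measures agree, and none of the three domains is put first.

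- **Burnout.** The MBI-SS is named as a primary measure, but not which of its scores. The instrument has three subscales; eligibility uses a total.
- **Wellbeing.** The PGWB short form, counted here as one score.
- **Academic achievement.** Three self-reported measures: exams passed, mean grade and a satisfaction rating.

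The section on statistical analysis fits a mixed model over T1, T2 and T3 to each outcome and tests the Time by Group interaction. It adds: "Our expectation is that PC and WL should differ at T2 and T3, but not at T1".

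The section on participants and sample size has one calculation. It starts "Assuming a medium effect size" (d = 0.50) and arrives at a "sample size of 128 participants (i.e., two groups of 64 students") "to achieve a power of 0.80 (α = 0.05"). No outcome or time point is attached to it, and 130 students are to be recruited. The discussion text that follows the analysis plan describes the design as adequately powered and counts this as a strength: "We also identified a large range of possible primary and secondary outcomes".

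**The concern.** Choosing the primary endpoint and sizing the trial for it belong together, and both are protocol decisions. Here the sizing covers one test, while several results hold primary status. The document does not fix which result decides efficacy, so this could be settled after the data are seen.

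Each way of settling it has a cost. If any one success is enough, the type I error of the efficacy claim exceeds the stated 0.05. If alpha is divided, or if all must succeed, the stated power of 0.80 no longer holds. The statement that the trial is adequately powered is therefore true of one test, but not of the set of primaries as declared.

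**Working it through.** **Inputs from the protocol.** d = 0.50, alpha 0.05, power 0.80, 64 per arm calculated, 65 per arm planned, three primary domains, two post-baseline time points. Sidedness is not stated.

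**Inputs assumed.** Correlations between outcomes, and between T2 and T3; ranges are shown.

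**1. The plan's own figure.** Two-sample t-test, two-sided 0.05, noncentrality d x sqrt(n/2). Solving for power 0.80 gives n = 63.77, so 64 per arm and 128 in total.
- Power at 64 per arm: 0.801. At 65 per arm: 0.808.
- A one-sided test needs only about 51 per arm, so the 128 corresponds to one two-sided test.

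**2. Number of primary scores.** MBI-SS 1 (total) or 3 (subscales) + PGWB-S 1 + achievement 3 = 5 to 7.

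**3. Type I error if any success counts.** For k independent tests the chance of at least one p < 0.05 is 1 - 0.95^k. Correlated values come from simulating equicorrelated normal test statistics (400,000 draws), with each score treated as one test.

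| Tests | Independent | Correlation 0.5 | Correlation 0.7 | Correlation 0.9 |
|---|---|---|---|---|
| 3 | 14.3% | 12.5% | 10.9% | 8.4% |
| 5 | 22.6% | 18.2% | 14.9% | 10.1% |
| 7 | 30.2% | 23.0% | 17.8% | 11.5% |

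These are two-sided rates. Counting only false results in favour of counseling, three tests give 1 - 0.975^3 = 7.3% if independent and 5.4% at correlation 0.7, against a nominal 2.5%. The relative inflation is about the same.

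**4. If T2 and T3 were tested separately.** With T2-T3 correlation 0.7, 5 and 7 scores give 28.8% and 35.6% at between-score correlation 0.5, and 23.5% and 27.9% at 0.7.

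**5. Power if alpha is split (Bonferroni, d = 0.50).**

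| Tests | Alpha each | Power at 65 per arm | Total N for 0.80 |
|---|---|---|---|
| 3 | 0.0167 | 0.66 | 172 |
| 5 | 0.0100 | 0.59 | 192 |
| 7 | 0.0071 | 0.55 | 204 |

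**6. Power if all three domains must succeed.** Take one test per domain and a true d of 0.50 in each. If the tests are independent, power is 0.808^3 = 0.53. Positive correlation raises this towards 0.808, which is reached only if the three tests always agree.

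**The case against.** The strongest reply is that this is a condensed article. A multiplicity procedure, the exact score for each instrument and the decisive contrast may all be in an analysis plan that is not shown. That stands as far as it goes: silence on multiplicity does not show that error is uncontrolled. It does not remove the point, because the co-equal primaries and the single-test sizing are fixed in this document, and a later alpha split would lose power as in step 5.

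Second, the inflation needs a rule that any one success counts, and no such rule is written. The hypothesis in the aims names improvement in all three domains, which can be read as a joint requirement. Type I error would then not exceed 0.05, and the problem would become one of power. This stands, so the error rates are conditional.

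Third, a reader might infer that 10 to 14 score-by-time results (5 to 7 scores at two time points) each count as primary. With independent tests that would give false-positive rates of 40% (1 - 0.95^10) to 51% (1 - 0.95^14). The documents do not support this as a working figure. The analysis section describes one interaction test per outcome, and repeated scores from the same students are not independent. Those figures are a ceiling.

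Fourth, a reader might see a contradiction between the pre-post comparison in the aims and the three time points in the analysis section. There is no clear conflict, since the period after counseling can include both T2 and T3. What is missing is a named primary time point.

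Finally, the power figures are for an unadjusted two-sample t-test with Bonferroni. The planned mixed model uses the baseline, and Holm or a fixed order costs less. The limitations text also already concedes limited power for smaller effects. These remarks soften the 0.66 but do not restore 0.80 by the plan's own calculation.

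**Conclusion.** The point holds in a conditional form. The protocol fixes three unranked primary domains, comprising 5 to 7 scores, and sizes the trial for one two-sided test.

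- **Any success counts:** about 11-14% for three tests and about 15-30% for 5 to 7 scores (two-sided, assumed correlation 0.7 to 0, one test per score). Rates are higher only if T2 and T3 are tested separately. False results in favour of counseling run at about half of these, against 2.5%.
- **Alpha split over three domains:** power about 0.66 at 65 per arm, with all 130 students complete and d = 0.50.
- **All must succeed:** error is controlled, but power falls below 0.80.

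It would go too far to say that the trial's error rate is inflated as a matter of fact, because the decision rule is not stated. It would also go too far to say that 128 was calculated for the MBI-SS at T2, because the sample-size section names neither.

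**What to change.** Name one primary endpoint and state that the 128 calculation and its 0.80 power apply to that endpoint alone. The natural choice is the MBI-SS total (Efficacy items reversed), PC versus WL at T2, two-sided alpha 0.05. The MBI-SS total already defines eligibility, and burnout is the trial's question. This is a recommendation, since the sample-size section does not itself make the choice.

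Make MBI-SS at T3, PGWB-S and academic achievement key secondary outcomes. Test them in a fixed order, or by Holm, only if the primary succeeds, and say where each of the three achievement measures stands. Report the MBI-SS subscales as supportive.

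The cost is a change of wording in the protocol and the registry entry, best made before outcomes are analysed. Alpha stays at 0.05, the 128 stands (power 0.801 at 64 per arm, 0.808 at 65), and no further participants are needed. The downside is that wellbeing and achievement claims become secondary and depend on the burnout result.
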